## Abstract

**Background:**

Despite the diffusion into practice of percutaneous closure of a patent foramen ovale (PFO) in patients with cryptogenic stroke (CS), the benefits have not been demonstrated, and remain unclear. For any individual presenting with a PFO in the setting of CS, it is not clear whether the PFO is pathogenically-related to the index event or an incidental finding. Further, the overall rate of stroke recurrence is low in patients with CS and PFO. How patient-specific factors affect the likelihood that a discovered PFO is related to an index stroke or affect the risk of recurrence is not well understood. These probabilities are likely to be important determinants of the benefits of PFO closure in CS.

**Design/Methods:**

The goal of the Risk of Paradoxical Embolism (RoPE) Study is to develop and test a set of predictive models that can identify those patients most likely to benefit from preventive treatments for PFO-related stroke recurrence, such as PFO closure. To do this, we will construct a database of patients with CS, both with and without PFO, by combining existing cohort studies. We will use this pooled database to identify patient characteristics associated with the presence (versus the absence) of a PFO, and to use this "PFO propensity" to estimate the patient-specific probability that a PFO was pathogenically related to the index stroke (Model #1). We will also develop, among patients with both a CS and a PFO, a predictive model to estimate patient-specific stroke recurrence risk based on clinical, radiographic and echocardiographic characteristics. (Model #2). We will then combine Models #1 and #2 into a composite index that can rank patients with CS and PFO by their conditional probability that their PFO was pathogenically related to the index stroke *and *the risk of stroke recurrence. Finally, we will apply this composite index to completed clinical trials (currently on-going) testing endovascular PFO closure against medical therapy, to stratify patients from low-expected-benefit to high-expected-benefit.

## Background

Approximately 40% of all strokes are classified as cryptogenic, meaning that the cause is unknown despite an extensive work up [1]. While patent foramen ovale (PFO) is a common and generally benign condition found on autopsy in about 25% of the population [2-4], approximately 40% to 50% of patients younger than age 55 with cryptogenic stroke (CS) have PFO on transesophageal echocardiography (TEE) [4-7]. Furthermore, a PFO is found more frequently in patients with CS than in patients with a known cause of stroke, even in the elderly patient[7-9], These association suggest that PFO has an etiological role in CS, presumably via paradoxical emboli (PE) (i.e. venous emboli that gain access to the arterial circulation through a PFO) [7]. Thus, many physicians will recommend PFO closure in patients, especially younger patients, who have had CS.

However, the benefit of PFO closure in patients with CS has not been demonstrated, and remains unclear. First, for a patient presenting with a PFO and a CS, it is not clear for that individual whether the PFO is causally related to the index event or whether it is an incidental finding, since PFOs are so common in the general population. Second, the overall rate of stroke recurrence is relatively low in patients with CS and PFO, ranging in studies from 0% to 12% per year, with an average annualized risk across studies of approximately 2% [4,5,10]. Thus, even rare but serious procedure- and device-related complications may be sufficient to nullify the benefit of percutaneous closure, especially if many who receive the device have index strokes unrelated to their PFO. A method is needed to identify patients with CS and pathogenic PFOs, especially those with a high risk of recurrence from patients with CS and incidental PFOs.

The theoretical rationale for the RoPE study has been described in prior work [7,11]. Briefly, the RoPE Study builds on prior work demonstrating the potential importance of risk modeling in the interpretation of clinical trials, where overall results may not reflect the benefits to individual patients [12-17]. In the setting of CS specifically, we have shown that the probability that an individual will have a PFO can be predicted (i.e. prior to TEE) based on the presence or absence of conventional stroke risk factors (e.g. age, presence of hypertension, diabetes, hypercholesterolemia, etc.) and other characteristics. We call the patient-specific probability of finding a PFO in the setting of CS the "PFO propensity". Using simple assumptions and Bayes' theorem, PFO propensity can be shown to be directly but not linearly related to the patient-specific PFO-attributable fraction (i.e. the probability that the PFO is pathogenic rather than incidental)-- as shown in the Figure 1. Thus, although it is not possible in the individual patient to determine with certainty whether a discovered PFO is incidental or pathogenic, it is nonetheless possible to construct mathematical models that can stratify patients by their likelihood that their stroke is PFO-related.

**Figure 1 F1:**
[figure not shown]
**PFO Propensity and the Probability that a Stroke is PFO-attributable**. We define PFO propensity as the probability of finding a PFO in a patient, based on patient-specific characteristics (such as age and the presence or absence of hypertension, diabetes and hypercholesterolemia). Through Bayes' theorem, it is directly (though non-linearly) related to the probability that a cryptogenic stroke is PFO-attributable (in patients with both cryptogenic stroke and PFO).

Additionally, while prior studies have had limited statistical power to develop predictive models that can predict stroke recurrence given the low frequency of this outcome, the RoPE Study aims to overcome this barrier by combining multiple large multicentered studies to yield a pooled database with a sufficient number of cerebrovascular outcome events to model recurrence risk.

The aim of the RoPE Study is to develop mathematical models that can be used to stratify patients by the joint probability that an index stroke is "PFO-related" and that the stroke will recur and to use these models to stratify patients in on-going clinical trials testing percutaneous closure, with the goal of informing patient-selection for PFO closure in clinical practice. The steps by which this will be accomplished are summarized in Figure 2, as well as in the specific aims below.

**Figure 2 F2:**
[figure not shown]
**Summary of RoPE Study**. Schematic summary of the Risk of Paradoxical Embolism (RoPE) Study.

## Design/Methods

The specific aims of the RoPE Study are:

1. To construct from existing cohort studies of patients with CS studied with TEE, both with and without PFO, the largest extant CS database, sufficiently robust to support predictive risk modeling.

2. To identify patient characteristics associated with the presence (versus the absence) of a PFO, and to use this "PFO propensity" to estimate the patient-specific probability that a PFO was pathogenically related to the index stroke. (Model #1)

3. To develop a predictive model to estimate patient-specific stroke recurrence risk based on clinical, radiographic and echocardiographic characteristics in patients with PFO and CS. (Model #2)

4. To develop a composite index based on Models #1 & #2 that can rank patients with CS and PFO by their conditional probability that the PFO was pathogenically related to the index stroke (Model #1) *and *the risk of stroke recurrence (Model #2).

5. To apply this composite index to patients in completed clinical trials (currently on-going) testing endovascular PFO closure against medical therapy, to stratify them from low-expected-benefit to high-expected-benefit.

### Aim 1: To construct the largest extant CS database from existing cohort studies of patients with CS studied with TEE for the presence/absence of PFO

Methods for pooling multiple independent studies have been previously described [18,19]. Steps include: 1) selection of participating clinical trials and databases; 2) development of a collaborative investigative team including clinicians, statisticians and programmers; 3) preliminary determination of the availability and characteristics of data in each of the component databases; 4) complete specification of the dependent (outcome) variable used in each study and in the pooled analyses; 5) determination and specification of the independent (explanatory) variables; 6) specification of the inclusion/exclusion criteria for the studies; 7) verification of variable definitions; 8) acquisition of new data if required; 9) checking for consistency of effects across study databases.

Based on our own literature search, a published literature review [4], and then subsequently on a published meta-analysis [10], we contacted all investigators with relevant data examining the rate of recurrent stroke in patients CS and PFO. This also yielded data examining the presence/absence of PFO in patients with CS. We obtained agreements to include 13 databases with over 2500 subjects, as shown in Table 1. This provides the basis of our power calculations for subsequent aims.

**Table 1 T1:** RoPE Database

Database	# of subjects	# w/PFO	# w/o PFO	RoPE Investigator
APRIS [6]	83	17	66	[name]
Bern (published) [30]	159	159	-	[name]
Bern (unpublished)	249	249	-	[name]
CODICIA [31]	486	266	240	[name]
PFO-ASA Study [5]	581	267	314	[name]
German Study [24]	1126	389	737	[name]
Lausanne	172	93	79	[name]
NOMASS [32]	60	23	37	[name]
PICSS [33]	250	98	152	[name]
Sapienza (unpublished)	343	133	210	[name]
				[name]
Toronto [34]	114	114	-	[name]
Tufts	140	140	-	[name]
Total Estimates*	2546	1484	1062	

Precise determination of inclusion/exclusion criteria, specification of the independent variables and specification of the dependent variable for each of the models are dependent on careful examination of each of the component databases for details of variable definition and missingness. s Consensus on the variables will be reached among RoPE Investigators for the final models. Provisional variable descriptions are provided below.

The RoPE Study will include patients with CS who have been examined for the presence of a PFO with either TEE or Transcranial Doppler (TCD) and the injection of bubbles. The preliminary definition of CS for the RoPE Study conforms to the Trial of ORG 10172 in Acute Stroke Treatment (TOAST) classification,[20] and requires a "complete work-up" (defined below) for the cause of the stroke. Cardioembolic stroke in this classification was considered "probable" if there was a high-risk source of embolism and "possible" for medium risk sources. This latter category includes PFO and atrial septal aneurysms (ASA). For the purposes of the RoPE Study, subjects with medium risk sources will be considered cryptogenic. The definition of stroke for the RoPE Study is *"a sudden onset neurological deficit in a vascular territory presumed to be due to focal ischemia*." If the deficit lasts for less than 24 hours, it must be accompanied by acute magnetic resonance imaging (MRI) or computer tomography (CT) changes in appropriate locations. If the deficit is greater than 24 hours, MRI or CT changes are not required. *A "complete work-up" *must include: 1) MRI *or *CT; 2) Vascular imaging - catheter angiography or angiography by MRI or CT; 3) Cardiac rhythm study: at least one electrocardiography (ECG), or documented Holter or telemetry.

In addition to excluding patients with stroke of known cause, patients included in the RoPE study must be worked up for the presence of a PFO with a TEE using intravenous injection of bubbles. Patients can be included in model #1 without a TEE, if they have had both transthoracic echocardiography [to rule out other potential cardioembolic sources] and TCD with bubbles (to establish the presence/absence of right-to-left shunting). Only patients with a TEE will be included in Model #2, since this model will require assessment of the presence/absence of ASA and PFO grading.

Table 2 shows provisional independent (predictor) variables that we anticipate will be important in both the prediction of the presence/absence of PFO, and also the risk of the outcome (recurrent ischemic stroke, as defined above). Of note, we anticipate that harmonization of databases may require the acquisition of new primary data, potentially from the following sources: 1) medical record review 2) rereading of TEE tapes; 3) rereading of neuroimages; 4) obtaining follow-up for recurrent events. In general, the reasons for needing additional primary data from a particular database may include: 1) missing data on a portion of patients; 2) differing variable definitions between databases; and 3) new data (variables) required not previously collected in a given database. Medical record review would be possible for clinical registries and TEE tapes and neuroimages are potentially available for most of the component databases. Based on the characteristics of any observed missing data we will investigate the use of imputation and replacement algorithms, or whether a component database needs to be excluded--although statistical methods to preserve data and power will be fully employed (such as imputation for independent variables). Because missingness of the dependent (outcome) variable poses more potential problems due to informative censoring, we intend to exclude any datasets for which less than 90% of patients have follow-up at one year. Re-adjudication of all stroke outcomes is planned as part of the RoPE study. Methods ensuring database quality during database construction will be complemented by steps taken during the predictive modeling process to check for consistency of effects across databases.

**Table 2 T2:** Initial RoPE Variables of Interest

Variable Type	Variable
**Clinical**	Age
	Gender
	Race
	History of the following (prior to index stroke)
	*Migraines*
	*Hypertension*
	*Diabetes*
	*Prior cerebral ischemia*
	*Coronary artery disease*
	*Obesity*
	*Hypercholesterolemia*
	*Smoking status*
	*Antithrombotic medications*
	*Deep vein thrombosis*
	*Pulmonary Embolism*
	*Hypercoagulable states*
	Antithrombotic medications after index event
	Outcome: National Institutes of Health Stroke Severity Score

**Echocardiographic**	Hypermobility of interatrial septum ("ASA")
	Interatrial shunting at rest (e.g. not during Valsalva maneuvers)
	Volume of interatrial shunt (e.g. max. bubbles in left atrium)
	Anatomical PFO size
	Spontaneous Doppler flow seen on color

**Radiological**	MRI/CT findings of cerebral infarct: yes/no (at index stroke)
	Number of prior cerebral infarcts
	Anatomical location of index and prior infarct(s)

### Aim 2: To identify patient characteristics associated with the presence (versus the absence) of a PFO, and to use this "PFO propensity" to estimate the patient-specific probability that a PFO was pathogenically related to the index stroke. (Model #1)

Since PFOs discovered in patients with CS may be pathogenically related to the stroke or not, in Aim 2, we will use logistic regression models to identify patient characteristics that are associated with the presence of a PFO among patients with CS ("PFO propensity"). In previous work [7,11,21], we have shown that this "PFO propensity" can be related to the probability that a PFO is pathogenic (i.e. non-incidental) using Bayes' theorem and 2 simple assumptions: 1) if not for those strokes that are PFO-attributable, the probability of a PFO in a CS patient would be the same as in the general population (controls); and 2) the rate of PFO-attributable strokes in PFO-negative CS patients is near-zero. Under these conditions:

Since the patient-specific probability of PFO in CS is given by the PFO propensity (i.e. the prevalence of PFO in CS patients otherwise similar to the patient), the only additional term needed to estimate the probability that a PFO is incidental for a particular patient is the general rate of PFO in the population (PFO probability in controls).

To develop a predictive model for PFO propensity, we will explore crude associations (overall and within each database) between the presence of a PFO and clinical variables including the subject's age, gender, race, hypertension, diabetes, hyperlipidemia, history of prior episodes of cerebral ischemia, obesity, antithrombotic medications, concurrent deep venous thrombosis, and neuroradiologic variables (i.e. prior stroke on MRI or CT, small [< 1.5 cm] versus large infarct, location of infarct). Multivariable associations between predictors and the presence of a PFO will be examined using logistic regression models. Selection of candidate variables for these models will be based on clinical rationale and the published literature. Variables with statistically marginal associations in the preliminary analyses (p > 0.15) will be removed. Non-linear associations between independent risk variables and the outcome will be investigated using generalized additive spline models[22]. As indicated, appropriate parametric logistic regression models will be developed to capture these non-linear relationships.

Statistical significance of individual variables in the final model will be assessed with the Score statistic. Based on clinical reasoning, a limited number of interaction terms between risk factors may also be tested for inclusion in the model. The models will be analyzed by conventional criteria, such as goodness-of-fit tests, and receiver operator characteristics (ROC) curve areas [23]. "Calibration" of predicted probabilities of outcome throughout the range of their predictions will be evaluated with plots. The final multivariable regression models will be run separately on each of the component datasets to assess the consistency of the results and model performance. Based on these results, interaction terms between indicator variables representing study and model predictors of PFO will be used to investigate significant variation in associations across study datasets. Predictors found to be inconsistent across studies may be removed from the model. We will reanalyze the data using a generalized linear mixed model that includes a random effect term for study to get final parameter estimates with their corresponding standard errors.

Adequacy of the Data for Aim 2: Based on a preliminary review of the included studies (see Table 1), we will have potentially 3,101 subjects available for the models predicting PFO (1,332 with and 1,769 without PFOs), drawn only from those databases enrolling all cryptogenic stroke patients with and without PFO. This sample size will provide 80% power to detect an odds ratio of 1.23 for a balanced risk factor. For a risk factor with a prevalence of 20%, this sample size will still provide 80% power to detect an odds ratio of 1.29. The study will still provide sufficient power to detect clinically relevant associations even in the presence of significant data being unavailable for modeling. For example, if we totally eliminate data from the largest RoPE component study (the German database [24]), we will have 1,975 included subjects (928 with and 1047 without PFOs.) This sample will provide 80% power to detect odds ratios of 1.29 and 1.38 for risk factors with a prevalence of 0.50 and 0.20, respectively. Since outcome data is not needed for this analysis, loss of this amount of data is unlikely and the database would anyway still have ample power, permitting full exploration of multiple variables.

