### Aim 3. To develop a predictive model to estimate patient-specific recurrence risk based on clinical, radiographic and echocardiographic characteristics in patients with PFO and CS. (Model #2)

For Aim 3 we will use Cox proportional hazard models to develop a predictive model to estimate patient-specific recurrence risk. Because patients with CS with higher PFO-related recurrence risk generally have a lower prevalence of conventional stroke risk factors[25], failure to adjust for general (non-PFO-related) recurrent risk can lead to paradoxical results. This has been a major challenge for prior studies, since the low rate of outcomes limits the statistical power to control for conventional stroke risk factors and model PFO-related risk. While in the RoPE study we will have many-fold the number of outcomes compared to any prior study, statistical power for this analysis remains an issue.

To address this, depending in part on the number of outcomes, we will consider a two-step approach, that takes advantage of the outcomes in the component of the RoPE database of CS patients *without *PFO. First, we will construct a model for recurrence risk on the component of the study of CS patients *without *PFO. Next, we will construct a model for recurrence risk on the component of the study of CS patients *with *PFO, using the derived risk variable from the first step to control for the confounding background risk of stroke from PFO-unrelated causes. This will permit background stroke risk to be controlled for in a statistically efficient fashion. For step two, using the study subjects with known PFO, we will pay particular attention to echocardiographic information (e.g. hypermobility of the interatrial septum, interatrial shunting at rest, severity of interatrial shunt, anatomical PFO size, presence/absence of spontaneous flow on color Doppler)--to identify features of "high-risk" PFOs.

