Preliminary analyses for both phases of this two step process (i.e. modeling recurrence risk in patients without PFO and modeling recurrence risk in patients with PFO) will investigate associations between established risk factors and recurrent strokes. Kaplan-Meier survival curves and logrank tests will be used to assess statistical significance. For each phase, a multivariable prediction model for recurrent stroke will be developed using a Cox proportional hazard model, using an approach otherwise similar to that described for Aim 2. Predictive discrimination will be assessed using the overall C index [26]. Model calibration is assessed by comparing predicted survival probabilities against Kaplan-Meier (observed) probabilities across equal-sized risk quantiles (based on predicted recurrence probabilities). Differences between predicted and observed probabilities will be compared using a modified Hosmer-Lemeshow χ^2 ^statistic [27]. The Cox models be re-run including the study as a stratification factor to control for potential between-study differences in baseline survival functions when estimating hazard ratios of potential risk factors.

Adequacy of the data for Aim 3: Power was calculated on extreme optimistic and extreme pessimistic calculations. To obtain outcome rates for our sample we used databases with patients who had PFOs. We optimistically estimate available follow-up data for up to 1,752 patients with PFO; 1,332 from databases with both PFO and non-PFO patients and an additional 420 from databases that only have data on patients with PFOs. Based on the average outcome rates on the observed data, the estimated stroke rate for these patients is 6%. The sample size of 1,752 will provide 80% power to detect a clinically relevant hazard ratio of 1.77 for a risk factor with a prevalence of 50% and an overall stroke rate of 6%. Most pessimistically, we excluded 100% of our largest study (the German study [24]) and estimated follow-up will only be available for 70% of the remaining subjects which would result in a total sample size of 944. With this extremely conservative estimate of the sample size the study will have 80% power to detect a hazard ratio of 2.22 assuming an overall stroke rate of 6% and a risk factor prevalence of 50%.

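### Aim 3 inherits a crude p > 0.15 screen that may drop high-risk PFO features before background stroke risk is adjusted for

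*Protocol article*

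**What the plan says.** Under Aim 2 (Model #1), the modelling starts from unadjusted associations: "we will explore crude associations (overall and within each database) between the presence of a PFO and clinical variables". The candidate list is set first ("Selection of candidate variables for these models will be based on clinical rationale and the published literature"), and a removal rule follows: "Variables with statistically marginal associations in the preliminary analyses (p > 0.15) will be removed".

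Under Aim 3 (Model #2), the preliminary analyses cover both phases, patients without and patients with a PFO. They "will investigate associations between established risk factors and recurrent strokes", and "Kaplan-Meier survival curves and logrank tests will be used to assess statistical significance". The multivariable Cox model for each phase is then developed "using an approach otherwise similar to that described for Aim 2". The 0.15 threshold is not repeated there.

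Aim 3 also explains why background risk matters. Patients whose recurrence risk is more PFO-related tend to carry fewer conventional risk factors, and "failure to adjust for general (non-PFO-related) recurrent risk can lead to paradoxical results". The proposed answer is a two-step approach, which the article says will be considered. A risk variable derived in patients without PFO enters the model for patients with PFO. Stratification by study is mentioned after that: "The Cox models be re-run including the study as a stratification factor".

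**The concern.** The order of the steps defeats their purpose. The background-risk variable is there to reveal PFO features whose effect is hidden because their carriers have low conventional risk. If the Aim 2 removal rule applies to the Aim 3 log-rank results, such a feature is judged on its unadjusted association and can be removed before the background-risk variable is in the model. Re-running the final Cox model with study strata cannot bring it back.

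Step two exists to identify the features of high-risk PFOs. A feature lost at the screen cannot enter the composite index of Aim 4, and so plays no part in the treatment-by-index interaction tested in Aim 5.

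**Working it through.** **The plan's own figures.** Aim 3 gives N = 1,752 and N = 944, a 6% stroke rate, 50% prevalence and 80% power for hazard ratios of 1.77 and 2.22.

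- Events: 1,752 × 0.06 = 105; 944 × 0.06 = 57 (the article says about 60).
- Freedman's formula, with two-sided alpha 0.05 assumed: power = Φ(√events × (HR − 1)/(HR + 1) − 1.96). This gives 81.3% for 1.77 with 105 events and 81.4% for 2.22 with 57.

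The stated power is sound, and the point here does not depend on it. The same event counts and the hazard ratio of 1.77 are used below.

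**What a crude screen sees.** Let feature X have true hazard ratio 1.77. Let Z be a background risk factor with hazard ratio HR_Z, present in a share q1 of carriers of X and q0 of non-carriers. With rare events,

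crude HR = 1.77 × [1 + q1(HR_Z − 1)] / [1 + q0(HR_Z − 1)].

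The test statistic has mean t = √(events × p(1 − p)) × |ln crude HR|, where p is the prevalence of X. The critical value for two-sided p = 0.15 is 1.44, so

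P(drop) = Φ(1.44 − t) − Φ(−1.44 − t).

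**Assumptions.** The documents give neither HR_Z nor the association between X and Z. The moderate to strong rows assume that Z is present in 50% of patients with HR_Z of 2 to 3. X is present in 55% of patients without Z and 35% with Z (so p = 0.45, q1 = 0.389, q0 = 0.591), or in 60% and 30% (p = 0.45, q1 = 0.333, q0 = 0.636). The first and last rows take p = 0.5 and bracket these.

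**One case in full** (HR_Z = 2.5, 60%/30%):

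- Crude HR = 1.77 × (1 + 0.333 × 1.5)/(1 + 0.636 × 1.5) = 1.77 × 1.500/1.955 = 1.36.
- 105 events: t = √(105 × 0.45 × 0.55) × ln 1.36 = 1.56, so P(drop) = 0.45.
- 57 events: t = 1.15, so P(drop) = 0.61.

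| Assumed confounding | Crude HR | P(drop), 105 events | P(drop), 57 events |
|---|---|---|---|
| Weak: HR_Z 1.5, q0 0.50, q1 0.45 | 1.73 | 8% | 26% |
| HR_Z 2, X in 55%/35% | 1.55 | 22% | 42% |
| HR_Z 2, X in 60%/30% | 1.44 | 33% | 52% |
| HR_Z 2.5, X in 60%/30% | 1.36 | 45% | 61% |
| HR_Z 3, X in 60%/30% | 1.30 | 54% | 67% |
| Extreme: HR_Z 4, q0 0.60, q1 0.20 | 1.01 | 85% | 85% |

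**The same threshold with adjustment** (p = 0.5). The hazard ratio stays at 1.77.

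- No information lost: t = √(105/4) × ln 1.77 = 2.93, P(drop) = 7%. With 57 events, t = 2.16, P(drop) = 24%.
- Allowing for correlation between X and Z: at q0 = 0.60 and q1 = 0.20 the squared correlation is (0.4² × 0.25)/(0.4 × 0.6) = 0.167, so effective events fall by one sixth. P(drop) becomes 11% and 30%.

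**A larger effect.** With a true hazard ratio of 2.22, 105 events, HR_Z = 2, q0 = 0.50 and q1 = 0.30, the crude hazard ratio is 1.92 and P(drop) is only 3%. The screen does harm when effects are moderate or events are few.

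**The case against.** The strongest reply is that the article never states this rule for Aim 3. The threshold appears once, under Aim 2, and reaches Aim 3 only by a general reference. The preliminary analyses in Aim 3 are said to concern established risk factors, while echocardiographic features are promised particular attention in a step-two model that does control for background risk. One can read this as screening conventional factors crudely and examining PFO features with adjustment. The article also recognises the confounding and offers a remedy for it.

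This limits the claim but does not remove it. The preliminary analyses are described for both phases, including patients with PFO. Table 2 lists the echocardiographic variables among the provisional predictors. Clinical rationale sets the candidate list, and the p > 0.15 rule then removes from it in mandatory terms. Particular attention is an intention and not a selection rule, and no sentence exempts these features.

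A reader might infer more than the text supports:

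- *That the screen removes exactly the PFO features, or that the article says they are masked.* It says only that unadjusted analysis can mislead. Removal is a probability that depends on unstated confounding.
- *That the log-rank tests are unstratified.* They are merely not described as stratified.
- *That variation between databases in PFO prevalence (Table 1), or the 0% to 12% annual recurrence in the Background, shows confounding by study here.* Every step-two patient has a PFO, so prevalence is not informative. The recurrence range comes from published studies, not from the component databases.
- *That Aim 2 needs the same change.* Aim 2 already looks within each database, tests study-by-predictor interactions and refits with a random study effect.

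**Conclusion.** The concern holds in a limited form. Taken together, the Aim 2 rule and the Aim 3 cross-reference put an unadjusted screen ahead of the adjustment that Aim 3 says is needed, and echocardiographic features are not exempt. The text permits this loss; it does not show that the loss will occur.

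The calculated loss rests on assumed confounding and a true hazard ratio of 1.77. Under moderate to strong negative confounding, the crude screen raises the chance of discarding the feature from about 7-11% to 22-54% with 105 events, and from about 24-30% to 42-67% with 57. These ranges are not bounds. Weak confounding leaves the chance near the adjusted figures (8% and 26%), and extreme confounding takes it to 85%. The change is worth making because it is cheap and the features at risk are the ones Model #2 is meant to find.

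**What to change.** In Aim 3 step two, state that the crude p > 0.15 screen does not apply to the pre-specified echocardiographic features. Assess them in a Cox model that includes the step-one background-risk variable and is stratified by study from the start, and make any selection within that adjusted model. No change to Aim 2 is needed.

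The cost is a few sentences and a few more parameters carried with about 57 to 105 events. The article already notes the risk of over-fitting at the lower figure. Shrinkage can handle this, for example a penalised Cox model that leaves the background-risk variable unpenalised.
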